### Strategies to improve adherence to interventions {11c}

To minimize the risk of missing data, each participant will be furnished with paper reminders containing precise dates and times for all scheduled sessions. Additionally, the investigator will conduct weekly phone calls to prompt participants about upcoming sessions and inquire about their adherence to medication.

### Relevant concomitant care permitted or prohibited during the trial {11d}

During the trial, there will be no regulations or restrictions placed on concomitant care or interventions.

### Provisions for post-trial care {30}

N/A. Given the low-risk nature of this study, we do not anticipate the necessity for posttrial care provisions.

### Outcomes {12}

The primary outcome of this study will be the END within 7 days. END will be defined as a 2-point increase in the NIHSS score or a 1-point increase in motor function (specifically NIHSS Items 5, 6, and 7) within 24 h to 7 days of AIS onset. To address the potential impact of END severity on the reliability of the primary outcome, we will conduct a sensitivity analysis using a higher threshold: a 4-point worsening in the NIHSS or a 2-point increase in motor function, which will be classified as severe END.

The secondary outcomes of the study will include:Evaluation the rate of good prognosis at 30 and 90 days. Good prognosis will be defined as a modified Rankin Scale (mRS) score of 2 or lower, which indicates either no disability or minor disabilityAssessment of the recurrence rate of symptomatic cardiovascular and cerebrovascular events within 90 daysAnalysis of changes in blood biochemical indices (including liver function, renal function, lipid profile, etc.) before and after treatment, measured at baseline, 7 days, 30 days, and 90 daysExamination of changes in inflammatory factors (interleukin-6, IL-6; interleukin-8, IL-8; tumor necrosis factor-alpha, TNF-α) before and after treatment, assessed at baseline and 7 days

Safety outcomes will be documented by recording the types and frequencies of all adverse events and abnormalities in laboratory tests throughout the study duration. Safety evaluations will include assessments of the patients’ general condition, vital signs, blood routine tests, blood biochemistry, liver and kidney function, coagulation function, and neuroimaging examinations. All participants will undergo assessments before treatment initiation and at the initial treatment milestones of 30 days and 90 days.

### Participant timeline {13}

The standard protocol is depicted in Fig. 2.

**Fig. 2 Fig2:**
[figure not shown]
Standard Protocol Items: Recommendation for Interventional Trials (SPIRIT). NIHSS, National Institutes of Health Stroke Scale; mRS, modified Rankin Scale; IL-6, interleukin-6; IL-8, interleukin-8; TNF-α, tumor necrosis factor-alpha

### Sample size {14}

This study is a randomized controlled trial with the intervention group as the PI group and the control group as the AT group. The study involves AIS patients with a confirmed history of CHD, and the primary outcome is the END in the two groups.

Based on our retrospective observation of 21 AIS patients with a history of CHD and no prior use of PCSK9 inhibitors, hospitalized at the First Affiliated Hospital of Dalian Medical University from April 2022 to June 2023, a total of 7 patients exhibited END within 24 h to 7 days of disease onset, accounting for 33.3%. During the same period, among 22 AIS patients with a history of CHD who were treated with PCSK9 inhibitors within 24 h of onset, 3 patients experienced END, accounting for 13.6%. Assuming the incidence of END in the intervention and control groups are 13.6% and 33.3%, respectively, with a two-sided α level of 0.05 and 80% power, we used the PASS software version 15 (NCSS, LCC, Taiwan 2017) to calculate the sample size. Each group requires 70 patients. Considering a 10% loss to follow-up, both groups will need 78 patients, making a total of at least 156 patients across both groups. The sample size calculation formula is as follows:$$n=2({Z}_{\alpha /2}+{Z}_{\beta }{)}^{2}\cdot p(1-p)\div (\delta {)}^{2}$$where:

*n* is the sample size per group.

*Z*_α_/2 is the critical value for a two-sided significance level (1.96 for *α* = 0.05).

Z_*β*_ is the critical value for power (0.84 for 80% power).

*p* is the estimated overall incidence rate.

*δ* is the expected difference between the two groups.

## Assignment of interventions: allocation

### Sequence generation {16a}

The allocation sequence for this study will be generated using computer-generated random numbers. The randomization will be stratified by gender. To reduce the predictability of the sequence, blocked randomization will be used to ensure a 1:1 ratio between the PI group (PCSK9 inhibitor with statin) and the AT group (statin monotherapy). Details of the block sizes and the randomization process will be documented separately and will remain unavailable to those who enroll participants or assign interventions.

### Concealment mechanism {16b}

The allocation sequence will be concealed using sequentially numbered, opaque, sealed envelopes. An independent researcher, not involved in recruitment, treatment, or assessment, will prepare these envelopes, each containing the group assignment (either the AT group or the PI group). After obtaining informed consent and completing baseline measurements, participants will be assigned the next sequential envelope by a designated researcher who is not involved in treatment or outcome assessment. The envelopes will remain sealed until the participant is assigned to an intervention, ensuring the allocation sequence is concealed from those enrolling participants and assigning interventions.

## Assignment of interventions: blinding

### Who will be blinded {17a}

Researchers responsible for data collection and outcome analysis will be blinded to group assignments until after data analysis is completed, as they will not be involved in participant assignment or intervention implementation.

### Procedure for unblinding if needed {17b}

Not applicable to study; the design is open label, so unblinding will not occur.

## Data collection and management

### Plans for assessment and collection of outcomes {18a}

The principal investigator will ensure that all study team members receive proper training, with access to written instructions and standard operating procedures. Regular meetings will facilitate communication and the sharing of new information. For quality assurance, the ethics committee (EKNZ) or an independent trial monitor may visit the research sites and will have direct access to source data and study-related files. All participant data will be kept strictly confidential and immediately uploaded to the designated cloud server after each assessment.

### Baseline

During the baseline assessment, demographic information will be gathered using standardized questionnaires. A comprehensive medical profile, including current and past treatments, allergies, personal background, surgical history, and family medical history, will be compiled. Assessments will include physical examinations and reliable laboratory tests (blood routine, urine routine, blood biochemistry, coagulation function, inflammatory factors). Additionally, electrocardiograms, NIHSS and mRS scores, documentation of concurrent medications, and recording of adverse events will be conducted.

### Treatment

Eligible patients will be randomly assigned to either the PI group (PCSK9 inhibitor combined with statin) or the AT group (statin monotherapy) to receive the designated interventions. On day 7 after enrollment, a physical examination and laboratory tests will be reassessed. The primary outcomes will be evaluated, mortality data collected, and concomitant medication usage documented.

### Follow-up

The follow-up period will start on day 8 after enrollment and continue until day 90, with evaluations on days 30 and 90. Assessments will include concomitant medications, adverse events, physical examinations, laboratory tests, NIHSS and mRS scores, and the occurrence of any recurrent cardiovascular or cerebrovascular events. If a participant experiences an endpoint event (recurrent cardiovascular or cerebrovascular event) during treatment or follow-up, the clinical study will be terminated, and active management will be initiated.

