## Statistical methods

### Statistical methods for primary and secondary outcomes {20a}

Once all participants have completed their assessments, data analysis will commence. To reduce bias, the data analyst will remain blinded during the analysis process. Only participants who strictly adhere to the intervention protocol will be included in the analysis. Data that are missing or deviate from the protocol will be excluded from the analysis.

The primary and secondary outcomes will be combined as dependent variables in the generalized linear model (GLM). First, a univariate analysis of the treatment groups will be performed to determine the unadjusted risk ratio (RR) and odds ratio (OR), along with a 95% confidence interval (CI). Next, continuous variables like the NIHSS score at admission, mRS score, and age will serve as covariates. Categorical variables such as sex, hypertension, diabetes, and prior strokes will be included as factors in the GLM to reduce variance error. If the outcomes show statistical significance for the main effects, interaction effects will be used to assess differences between the groups. Changes in blood biochemical indices will be analyzed using repeated measures ANOVA or mixed-effects models, accounting for measurements taken at baseline, 7 days, 30 days, and 90 days. Changes in inflammatory factors (IL-6, IL-8, TNF-α) from baseline to 7 days will be evaluated using paired *t*-tests or Wilcoxon signed-rank tests, based on data distribution. Sensitivity analysis will use the criterion for severe END, defined as either a 4-point increase in NIHSS or a 2-point worsening in motor function based on a higher threshold. All analyses will be conducted using SPSS (IBM Corp., Armonk, NY, USA), with a significance threshold of *α* = 0.05.

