### Adverse event reporting and harms {22}

Adverse events (AEs) are defined as any clinical manifestation, syndrome, or worsening of pre-existing conditions that affect the health of participants during the clinical trial. These events may not necessarily be related to the PCSK9 inhibitor and statin treatment and can include new illnesses or exacerbation of existing symptoms. All solicited and spontaneously reported AEs, as well as other unintended effects of trial interventions or conduct, will be documented from participant enrollment until the study concludes. All AEs will be recorded in the electronic case report form (eCRF). Participants will be monitored for AEs through regular visits, phone calls, and during any unscheduled visits. The study team will assess AEs for severity, duration, and causality. The severity of AEs will be classified according to the Common Terminology Criteria for Adverse Events (CTCAE), and causality will be determined based on the relationship between the AE and the study intervention, categorized as unrelated, unlikely, possible, probable, or definite. Serious adverse events (SAEs) will be reported to the ethics committee and relevant regulatory authorities within 24 h of awareness by researchers. Following the occurrence of an SAE, researchers must provide appropriate treatment to the participant and submit a follow-up report to the ethics committee within 15 days, detailing the cause of the event and the measures taken.

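### A recurrent event ends a participant's study with no provision for later outcome assessment, so day-30 and day-90 mRS can go missing because of an outcome

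*Protocol article*

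**What the plan says.** All references are to the Protocol article.

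- **Follow-up (under {18a}).** This phase starts on day 8 and is to "continue until day 90, with evaluations on days 30 and 90". NIHSS, mRS, laboratory tests, adverse events and recurrent events are listed for those visits. The section then adds: "If a participant experiences an endpoint event (recurrent cardiovascular or cerebrovascular event) during treatment or follow-up, the clinical study will be terminated". The rest of that sentence concerns the clinical management of the event.
- **Outcomes {12}.** One secondary outcome is "Evaluation the rate of good prognosis at 30 and 90 days". The cut-off for that outcome is set on the disability scale: "Good prognosis will be defined as a modified Rankin Scale (mRS) score of 2 or lower". Recurrent symptomatic cardiovascular and cerebrovascular events to day 90 are another secondary outcome, so the event that ends participation is itself an endpoint. Safety is to be recorded over the whole study.
- **Treatment.** At day 7, "The primary outcomes will be evaluated, mortality data collected, and concomitant medication usage documented". END is a NIHSS worsening "within 24 h to 7 days of AIS onset".
- **{18b}** aims for complete follow-up through contact, flexible visits and reminders. It does not mention participants whose study has been ended.
- **{22}.** Adverse events "will be documented from participant enrollment until the study concludes".
- **{20a}.** "Data that are missing or deviate from the protocol will be excluded from the analysis".
- **{20c}.** The primary outcome uses an ITT set and the secondary outcomes a per-protocol set. Multiple imputation is planned only if more than 10% of data are missing.

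**The concern.** Ending the clinical handling of a participant and ending outcome assessment are different things, and the Follow-up sentence does not separate them. If assessment stops at the event, whether mRS is observed depends on having had a recurrence, and recurrence plausibly predicts an mRS above 2. The missing values are then informative because of the design, not because of chance dropout.

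Two things are at stake. First, the good-prognosis rate would be too high in each arm. Second, the comparison between arms would be made largely among event-free participants. Benefit on mRS that works through preventing recurrences would be weakened in that comparison, although the Background gives fewer cardiovascular events as part of the drug's promise. Assessments that were never made cannot be recovered at the analysis stage.

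**Working it through.** **The plan's own figure.** The article gives no recurrence rate, so nothing on this exact point can be reproduced. The sample size in {14} can be. With 13.6% vs 33.3%, two-sided alpha 0.05 and 80% power, the unpooled variance gives 68.7 (69) per group and the pooled test 72, against the stated 70. Then 70 / 0.90 = 77.8, so 78 per group and 156 in total. Power at 70 per group is 79%. This point does not dispute those figures.

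**Good prognosis, one arm.** Let e be the proportion with an event, g0 the proportion with mRS 2 or lower if event-free, and g1 the proportion after an event.

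- True rate = (1 - e) x g0 + e x g1
- Rate seen if participants with events are dropped = g0
- Overstatement = e x (g0 - g1)

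Assumed: g0 = 60-70%, g1 = 20-30%, so g0 - g1 = 30 to 50 points.

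| Assumed e | Overstatement | Participants affected (of 156) |
|---|---|---|
| 5% | 0.05 x 30 to 50 = 1.5 to 2.5 points | 7.8, about 8 |
| 10% | 3.0 to 5.0 points | 15.6, about 16 |
| 15% | 4.5 to 7.5 points | 23.4, about 23 |

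This treats every event as a lost mRS value. Fatal events scored as 6 would reduce the overstatement. An event after day 30 costs only the day-90 value.

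**Good prognosis, between arms.** Suppose the drug affects mRS only through recurrence.

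- 10% (AT) vs 5% (PI): true difference = 0.05 x 30 to 50 = 1.5 to 2.5 points. Missing: 7.8 + 3.9 = 11.7 of 156 (7.5%).
- 15% vs 5%: true difference = 0.10 x 30 to 50 = 3.0 to 5.0 points. Missing: 11.7 + 3.9 = 15.6 of 156 (10.0%).

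In both cases the difference among event-free participants is 0, and missingness from events alone does not exceed the 10% trigger for imputation. Up to 15 participants (15 / 156 = 9.6%) can be lost this way without triggering it. Above the trigger, imputation would have few or no observed mRS values after a non-fatal recurrence to learn from.

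**END.** The assumption least favourable to the plan is that every early event would have met END, that END had not yet been recorded, and that the participant is dropped. Remaining rate = (END rate - removed) / (1 - removed).

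| Removed AT / PI | END, AT vs PI | Difference | Risk ratio | Power |
|---|---|---|---|---|
| none | 33.3% vs 13.6% | 19.7 points | 0.136 / 0.333 = 0.408 | 79% |
| 5% / 2% | 0.283 / 0.95 = 29.8% vs 0.116 / 0.98 = 11.8% | 18.0 points | about 0.397 | about 73% |
| 2% / 2% | 0.313 / 0.98 = 31.9% vs 11.8% | 20.1 points | 0.116 / 0.313 = 0.371 | 82% |

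Power is for 70 per group less those removed. The difference can shrink or grow, and in both examples the risk ratio moves slightly away from 1.

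**The case against.** The sentence is ambiguous. Literally it could stop the whole trial, and a reader might infer that. The condition concerns one participant and is followed by that participant's management, so the text does not support that reading. It could also mean only that protocol treatment ends. The retention aim in {18b} and the adverse-event rule in {22} would fit that. This part of the objection stands: the article does not say that everything after the event is lost, only that nothing provides for collecting it. The wording in {22} does not settle the matter either, because it is unclear whether the study concludes for the trial or for the participant.

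A reader might infer that all benefit through recurrence disappears from the trial. It does not. Recurrence is its own secondary outcome and the terminating event is what it counts. A fatal event has an mRS of 6 by definition (NIHSS and mRS section). What can be weakened is the reflection of non-fatal recurrences in mRS.

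A reader might also infer that exclusion of missing data always applies. In a scenario such as 15% vs 8%, 11.7 + 6.2 = 17.9 of 156 (11.5%) would be missing, which passes the 10% threshold in {20c} and calls for imputation. So a flat statement that the arms would then look identical is not what the plan describes, although imputation would have little to work from.

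Finally, a reader might infer that the primary outcome is seriously compromised. That needs several assumptions together: an event before the day-7 evaluation, END not already recorded, the event meeting the NIHSS criterion, and the participant dropped despite the ITT set in {20c}. A cardiac event need not change the NIHSS, and nothing says that a worsening seen at the time of an event goes unrecorded.

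**Conclusion.** The point holds as a should-fix. On its sensible reading, the Follow-up sentence ends a participant's study because of an outcome, and it is not reconciled with Outcomes {12}, {18b} or {22}. The firm consequence concerns a secondary outcome. If patients fare worse after a recurrence, good prognosis is overstated in each arm, by about 1.5 to 7.5 points under the assumed 5-15% event rates and mRS rates above. Any mRS benefit acting through fewer recurrences is attenuated. The direction within each arm needs only worse outcomes after an event; the effect on the comparison depends on event rates by arm, which are unknown. Neither exclusion of missing data nor the per-protocol set repairs this, and imputation is unlikely to. An effect on END is possible but conditional and probably small, so the documents do not support calling the primary result unsafe on this ground.

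**What to change.** Leave the clause on clinical management of the event as it is, and reconcile the Follow-up section with Outcomes {12}, {18b} and {22}. Add a separate statement along these lines:

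> A recurrent cardiovascular or cerebrovascular event does not end outcome assessment. Day-7 NIHSS and END, day-30 and day-90 mRS, adverse events and vital status are collected at the scheduled visits for every randomised participant, whether or not study treatment continues.

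Also make clear that the sentence concerns the participant and not the trial, and that adverse-event recording in {22} runs to the participant's day 90. How an event is treated remains outside this point.

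The cost is a wording change through the amendment route already described in {25}, plus completion of scheduled visits for an assumed 8 to 23 participants. No new procedure is needed and the sample size stays at 156. Some of these participants may be harder to assess after an event, so a few values may still be missing.

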### Criteria for discontinuing or modifying allocated interventions {11b}

Participants are allowed to withdraw from the study at any time due to various reasons, including failure to meet the inclusion criteria, inability to continue with the intervention treatment, or participant request.

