### NIHSS and mRS

The National Institutes of Health Stroke Scale (NIHSS) and the modified Rankin Scale (mRS) are standardized tools for evaluating stroke severity and outcomes. The NIHSS assesses various neurological functions such as consciousness, vision, motor function, sensation, speech, and language. Scores range from 0 to 42, with higher scores indicating more severe impairment [18]. Motor function is specifically assessed through Item 5 (Motor Arm), Item 6 (Motor Leg), and Item 7 (Limb Ataxia). The mRS evaluates disability and dependence in daily activities, ranging from 0 (no symptoms) to 6 (death). In this study, validated Chinese versions of both scales will be used [19]. Assessments will be conducted by two independent neurologists, and if discrepancies arise in their scores, a third senior neurologist will be consulted for the final assessment. All raters will receive comprehensive training before the trial begins, and repeated measurements will be conducted to ensure reliability and accuracy.

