### Methods in analysis to handle protocol non-adherence and any statistical methods to handle missing data {20c}

To address protocol non-adherence, we will define the analysis populations as follows: the intention-to-treat (ITT) population will include all randomized participants who have at least one treatment record and will be used for analyzing the primary outcome. The per-protocol (PP) population will include only those participants who fully adhere to the study protocol without major deviations and will be used for analyzing the secondary outcomes. Experience indicates that dropouts are rare. If the proportion of missing data exceeds 10%, multiple imputation techniques will be employed to ensure the robustness of our study results.

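### Read as written, a recurrent vascular event ends the participant's study, so later mRS and events go uncollected and good prognosis is estimated mainly in event-free participants

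*Protocol article*

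**What the plan says.** The Follow-up section (under 18a) has participants "continue until day 90, with evaluations on days 30 and 90", with mRS, NIHSS, laboratory tests, adverse events and recurrent events assessed at those visits. It then sets a stopping rule. The trigger is a new vascular event, cardiac or cerebral, which the section itself counts as an endpoint, and the rule reads: "during treatment or follow-up, the clinical study will be terminated, and active management will be initiated". The sentence concerns a single participant's event, so I read it as ending that participant's study.

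Outcomes {12} lists "Evaluation the rate of good prognosis at 30 and 90 days" (mRS of 2 or lower) as a secondary outcome, and the rate of symptomatic recurrent vascular events within 90 days as another. Its safety paragraph has all participants assessed at 30 and 90 days. Trial design {8} schedules days 1, 7, 30 and 90 without exception.

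The section on discontinuing interventions {11b} lists "inability to continue with the intervention treatment" among the reasons for which a participant may withdraw from the study.

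On analysis, 20a states: "Data that are missing or deviate from the protocol will be excluded from the analysis". In 20c the per-protocol population "will be used for analyzing the secondary outcomes", the ITT population serves the primary outcome, and multiple imputation applies only if more than 10% of data are missing.

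**The concern.** The event that ends participation occurs after randomisation, is a named outcome, and is one the drug is expected to influence: the background section gives reduction of cardiovascular events as part of the rationale. A recurrent stroke or cardiac event also plausibly worsens disability. Whether a later mRS is missing therefore depends on both treatment and prognosis.

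Good prognosis at 30 and 90 days would then be compared mainly among participants who had no event. Any benefit or harm that acts through recurrence drops out of that comparison. The recurrence outcome would count at most one event per participant.

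The primary outcome is exposed to a lesser degree. The Treatment section runs to the day-7 evaluation and follow-up begins on day 8, so an event during treatment falls inside the END window.

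**Working it through.** **Side-by-side reading.** The stopping rule ends the study, not only the study drug. No section expressly provides for an mRS after the event. The retention plan {18b} is general and does not mention these participants. The consent provision {26b} covers continued use of data after withdrawal, not continued collection. The all-participant schedules in {8} and {12} conflict with the stopping rule, and nothing says which prevails.

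**What is lost.**
- Non-fatal event before day 30: the day-30 and day-90 mRS.
- Non-fatal event after day 30: the day-90 mRS only.
- Either case: any later recurrent events.
- Event in the first week: possibly the day-7 END evaluation, unless a qualifying NIHSS rise is already recorded.

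**Size.** The protocol has no figure of its own on this point. The only input taken from it is 78 participants per arm (Sample size {14}: 70 / 0.9 = 77.8, rounded up to 78; 156 in total). All other inputs are assumptions:
- r, the 90-day rate of events after which mRS is lost: 5-15% per arm.
- q0, good mRS without an event: 70%, the same in both arms.
- q1, good mRS with an event: 20-40%, the same in both arms.

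Rate with full follow-up = (1 - r) × q0 + r × q1.
Rate among those who stay = q0 = 70%.
Overstatement in an arm = r × (q0 - q1).
Hidden difference = (r_AT - r_PI) × (q0 - q1).

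Overstatement runs from 0.05 × (0.70 - 0.40) = 1.5 points to 0.15 × (0.70 - 0.20) = 7.5 points.

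| Event rate AT / PI | Lost, of 156 | Full follow-up AT | Full follow-up PI | Difference with full follow-up | Difference among those who stay |
|---|---|---|---|---|---|
| 5% / 5% | 7.8 (5.0%) | 67.5-68.5% | 67.5-68.5% | 0 | 0 |
| 10% / 5% | 11.7 (7.5%) | 65.0-67.0% | 67.5-68.5% | 1.5-2.5 points | 0 |
| 15% / 5% | 15.6 (10.0%) | 62.5-65.5% | 67.5-68.5% | 3.0-5.0 points | 0 |
| 15% / 8% | 17.9 (11.5%) | 62.5-65.5% | 66.0-67.6% | 2.1-3.5 points | 0 |
| 10% / 10% | 15.6 (10.0%) | 65.0-67.0% | 65.0-67.0% | 0 | 0 |

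Worked row, 10% / 5% with q1 = 20%: AT 0.90 × 0.70 + 0.10 × 0.20 = 0.650; PI 0.95 × 0.70 + 0.05 × 0.20 = 0.675; difference 2.5 points.

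**Do the analysis rules repair it?** In four of the five rows the loss from this source alone does not exceed 10%, so it would not by itself trigger imputation. Where imputation is triggered (11.5%), almost no post-event mRS has been observed to inform it, so it would borrow from event-free participants. Exclusion of missing data and the per-protocol population work in the same direction as the loss.

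**The case against.** The strongest reply is that ending the study is paired with starting active management, so the authors may have meant only that the study regimen stops. The all-participant schedules in {8} and {12}, adverse-event recording until the study concludes {22} and the aim of complete follow-up {18b} lean that way. This stands as a possible intent, but the text does not say so, and staff following the sentence literally would stop visits. On either reading the sentence needs correcting.

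A reader might infer that the rule removes exactly the participants with the worst prognosis. The documents do not support that: a participant with severe END and no recurrence stays in, and a fatal event can still be scored, since the mRS is described as "ranging from 0 (no symptoms) to 6 (death"). Nor does the rule simply wipe out END after an early recurrence: the END definition does not exclude NIHSS rises caused by recurrent stroke, so such an event may itself count. And 11b only permits withdrawal when treatment cannot continue; it does not remove participants automatically.

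The illustration also has limits. It sets mRS in event-free participants equal in the two arms, so treatment acts only through recurrence. Benefit through fewer END events, the trial's main hypothesis, would remain visible. The hidden 1.5-5 points should be set against a standard error of about √(2 × 0.70 × 0.30 / 78) = 7.3 points for this secondary outcome. All of this stands and bounds the size of the problem; it does not remove it.

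**Conclusion.** The concern holds as a defect in the outcome-collection rule. On its face the protocol stops observation at an outcome-related event, contradicts its own all-participant schedule, and has no analysis rule that repairs the loss. Under the assumed rates, good prognosis is overstated by about 1.5-7.5 points per arm, and about 1.5-5 points of between-arm difference are hidden when event rates differ. With equal event rates, and equal mRS distributions given event status, the difference is roughly unbiased although both rates are too high. The effect falls mainly on secondary outcomes and is smaller than one standard error; the effect on END is confined to first-week events and cannot be sized from the document. It is still worth correcting now, because outcomes that are never collected cannot be recovered at analysis.

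**What to change.** In the Follow-up section and in 11b, separate stopping allocated treatment from ending observation. State that scheduled outcome assessment (NIHSS to day 7; mRS, recurrent events, vital status and safety to day 90) continues for every randomised participant after a recurrent event or after stopping treatment, unless consent is withdrawn. Reconcile the stopping sentence with the schedules in {8} and {12}.

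The cost is a short amendment. The day-7, day-30 and day-90 visits are already scheduled and the sample size does not change. Under the scenarios above, about 8 to 18 participants would stay in follow-up. Clinical management of the event is not addressed here.
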